#### Data collection

Patient data will be collected by the investigator (or representatives) via an electronic Care Report Form (e-CRF) provided by the Institut Claudius Regaud Data Management Department. The e-CRF is based on ENNOV Clinical® software edited by Ennov Company. It is available on the secure website. Study data validation will be carried out to verify the completeness, the accuracy and consistency of data collected in the e-CRF. Data clarification forms will be issued by the Data Management Department of ICR in order to allow investigators sites to resolve data deficiencies and/or in accuracy.

### Sample size calculation

Based on the literature, we expect 25% of patients to present with a pain decrease of at least two points [6]. To detect a 25% improvement (i.e., standard: 25%, experimental: 50%), using a one-sided chi-square test with an alpha of 0.05%, will require the enrollment of 125 patients, for 90% power. Assuming that 5% of patients will be lost to follow-up, we will need to randomize 130 patients (Randomization ratio1:1). According to the recommendations for comparative phase II trials, the target differences and type I error rates are relaxed.

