**Methods:**

TEC-ORL is a parallel, multicenter randomized comparative phase II study evaluating whether Capsaïcin patches (Qutenza®) reduce neuropathic pain when compared to Amitriptyline (Laroxyl®) in head and neck cancer survivors presenting with neuropathic pain sequelae. The primary efficacy outcome is the rate of patients with a pain reduction of at least two points at 9 months compared to baseline. Assuming that 5% of patients become lost to follow-up, 130 patients will need to be randomized to detect a 25% improvement (i.e., standard: 25%, experimental: 50%) using a one-sided chi-square test with an alpha of 0.05%. According to the recommendations for comparative phase II trials, the target differences and type I error rates are relaxed. Randomized patients will either be treated with a capsaicin 8% (Qutenza®) patch applied at three time intervals in the experimental arm or with Amitriptyline (Laroxyl®) (oral solution 40 mg/ml) taken for 9 months at the recommended daily dose of 25 mg to 75 mg in the control arm.

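### The one-sided alpha is printed as 0.05%, but 125 patients at 90% power requires 5%; at 0.05% the power would be about 34%

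*Protocol article*

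**What the plan says.** The Sample size calculation section sets the effect with "To detect a 25% improvement (i.e., standard: 25%, experimental: 50"% and continues: "using a one-sided chi-square test with an alpha of 0.05%, will require the enrollment of 125 patients, for 90% power". The Abstract (Methods) has the same clause, "using a one-sided chi-square test with an alpha of 0.05", again followed by a percent sign. No other alpha is given anywhere in the article.

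The sample-size section then allows for attrition: "Assuming that 5% of patients will be lost to follow-up, we will need to randomize 130 patients", allocated 1:1. It closes by saying that, in line with recommendations for comparative phase II trials, "the target differences and type I error rates are relaxed".

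The Main statistical analysis section plans one-sided 95% confidence intervals for the response rates, and also for the odds ratio from a logistic model adjusted for the stratification factors. It does not state in words what result counts as success.

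**The concern.** An alpha of 0.05% is 0.0005, which is 100 times stricter than 0.05. It conflicts with three other statements in the article: the stated size and power, the claim that type I error has been relaxed, and the one-sided 95% intervals, which correspond to a one-sided 5% test.

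The printed alpha is the only explicit type I error level, so it is what a reader would take as the pre-specified threshold. A one-sided p-value of 0.01 fails at 0.05% and passes at 5%. The intended level can be inferred, but a pre-specified threshold should not have to be inferred once results are known.

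**Working it through.** **Inputs** (all from Sample size calculation): control rate p1 = 0.25; experimental rate p2 = 0.50; one-sided chi-square test; 90% power; 1:1 allocation; 5% lost to follow-up. The only quantity varied is alpha: 0.05 or 0.0005.

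**Formula** (pooled variance under the null, no continuity correction):

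n per arm = [z(1−α)·√(2·p̄·q̄) + z(0.90)·√(p1q1 + p2q2)]² / (p2 − p1)²

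with p̄ = 0.375, √(2 × 0.375 × 0.625) = 0.6847, √(0.1875 + 0.25) = 0.6614 and z(0.90) = 1.2816.

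**Step 1: reproduce the plan's 125, using α = 0.05 (z = 1.6449).**
- (1.6449 × 0.6847 + 1.2816 × 0.6614)² / 0.0625 = 1.9738² / 0.0625 = 62.34 per arm.
- The total is 124.7, or 125 when rounded up. Rounding each arm up gives 63 + 63 = 126. The arcsine formula gives 124.9.

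**Step 2: alpha as printed, α = 0.0005 (z = 3.2905).**
- (3.2905 × 0.6847 + 1.2816 × 0.6614)² / 0.0625 = 3.1005² / 0.0625 = 153.8 per arm.
- That is 154 per arm, or 308 in total.

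**Step 3: power with 125 patients (62.5 per arm).** Power = Φ{[0.25·√62.5 − z(1−α)·0.6847] / 0.6614}.
- α = 0.05: Φ[(1.9764 − 1.1262)/0.6614] = Φ(1.285) = 90.1%.
- α = 0.0005: Φ[(1.9764 − 2.2529)/0.6614] = Φ(−0.418) = 33.8%.

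**Step 4: does another formula rescue the printed alpha?**

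| Method | N for 90% power, one-sided 0.0005 | Power at 125, one-sided 0.0005 | N for 90% power, one-sided 0.05 |
|---|---|---|---|
| Pooled | 308 | 33.8% | 126 |
| Continuity-corrected | 324 | 27.1% | 142 |
| Unpooled | 294 | 38.1% | 120 |
| Arcsine | 305 | not computed | 125 |

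Totals are from per-arm rounding, except arcsine. Exact enumeration of the one-sided pooled test with 62 and 63 patients per arm gives 34.3% to 34.8% power at 0.0005, and 89.9% to 90.2% at 0.05. A two-sided 5% test needs 154 patients (pooled) and has 83.1% power at 125. Of the combinations tried, only one-sided 5% (pooled or arcsine) reproduces 125.

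**Step 5: allowance for loss.**
- 125 / 0.95 = 131.6, so 132 rather than 130.
- 130 × 0.95 = 123.5 evaluable, or 61.75 per arm. At α = 0.05, power = Φ[(1.9645 − 1.1262)/0.6614] = 89.8%.

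**The case against.** The strongest reply is that this is a plain misprint. The size, the power, the relaxed type I error and the one-sided 95% intervals all point to 5%; only the percent sign points elsewhere. The 34% therefore describes a trial nobody planned, and a p-value of 0.01 would in practice be judged against the 95% interval, which would exclude an odds ratio of 1. A formal success rule may also sit in the full protocol or analysis plan.

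Much of this stands. The design and the number of patients are sound at 5%, and the 34% measures how far the printed figures are from agreeing, not the intended trial's power. The 125 is also matched only to within rounding under per-arm rounding, and the 130 versus 132 point is negligible alone.

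What does not stand is that the text can be left alone. The intervals imply 5% but are not presented as a decision rule, while the explicit alpha says 0.05% in both places where it appears. Whatever another document may say, this article states the error level wrongly.

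**Conclusion.** The point holds. As printed, alpha, sample size and power are incompatible: 125 patients at 90% power corresponds to a one-sided 5% level. At 0.05% the requirement would be 308 patients (294 to 324 across one-sided formulas), and 125 would give 33.8% power (27% to 38%). This rests only on the article's own rates, sidedness and allocation. That 5% was intended is an inference, but every other relevant statement supports it. If it is right, no redesign is needed. The shortfall in the loss allowance is real but trivial: 89.8% power against 90%.

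**What to change.** In the Abstract and in Sample size calculation, replace 0.05% with a one-sided type I error of 5% (0.05). State once that success means a one-sided p-value below 0.05 for the treatment effect in the adjusted logistic model. That agrees with the one-sided 95% interval for the odds ratio already planned. In the same edit, either give 132 as the number to randomise, or keep 130 and report about 89.8% power after 5% loss.

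The cost is a wording correction. The analysis does not change. The sample size stays the same if 130 is kept and rises by two if 132 is chosen.

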### Main statistical analysis

The primary endpoint will be analyzed on the Intent To Treat population and expressed as values and percentages with 95% one-sided confidence intervals. Treatment effect will be estimated using a logistic regression model adjusted for stratification factors [19]. Odds ratios will be estimated with their 95% confidence intervals (one sided). The sensitivity analysis will be conducted using a similar method. Depending on the extent of missing data, the following complementary analyses may be conducted to evaluate its influence on the results of the study: case complete study, multiple imputation for missing data.

## Discussion

As the population of head and neck cancer survivorship increases, it has become increasingly important for health care providers to propose an optimized treatment for neuropathic pain. There is an unmet need for well-designed, robust clinical trials to help improve therapeutic strategies in this setting. Single arm trials, introduce several forms of bias including patient selection, and misspecification of the hypothesis. We therefore opted for a randomized comparative phase II TEC-ORL trial design. Randomized comparative trials are an essential tool to evaluate therapeutic strategies and new treatments. However, designing and conducting a randomized trial on supportive care for neuropathic pain is associated with several challenges [20]. Several new treatments that appeared effective in phase 2 trials subsequently failed to confirm efficacy in phase 3 registration trials. This may be explained by the application of restrictive inclusion criteria in the phase 2 trial to maximize treatment effect differences, but this approach ultimately impedes the external validity, and/or generalizability of the phase 2 trial. Restricted inclusion criteria may also potentially limit the relevance of randomized controlled trial results to ‘real-world’ practices and make patient recruitment difficult [21]. The primary reason for integrative pain trial failure is inadequate patient recruitment numbers. As cancer pain management takes place in the context of multiple, sometimes competing personal interests, the primary reason for non-participation is due to the patient and/or investigator. The other challenge is the poor retention of participants in pain trials, which may lead to missing outcome data and may introduce bias and reduce study power. In this setting, there is a need for specific strategies to improve the recruitment and retention of participants in randomized trials.

Neuropathic pain is common in cancer survivorship and is one of the most distressing symptoms for patients previously treated for head and neck cancer. Neuropathic pain also decreases quality of life. There is a need to provide optimal first-line treatment to reduce neuropathic pain and to limit chronic opioid use for post-treatment neuropathic pain management [10]. To the best of our knowledge, TEC-ORL is the first randomized comparative phase II trial investigating the activity of high-concentration capsaicin patches as a first-line therapy for head and neck cancer survivors presenting with neuropathic pain sequelae.

## Data Availability

Data sharing is not applicable to this article as no datasets were generated or analyzed during the current study.

## Abbreviations

NCI: National Cancer Institute
CTCAE: Common Terminology Criteria for Adverse Events
TRPV1: Transient Receptor Potential Vanilloid-1
NPSI: Neuropathic Pain Symptom Inventory
EORTC: European Organisation for Research and Treatment of Cancer
QLQ-C30: Quality of life Questionnaire Core 30
AE: Adverse event
